### Recruitment strategy

The recruitment process started in October 2015 and will end in September 2020. Forty-eight participants will be randomly assigned into either NMES + FES or Control + FES groups for 24 weeks. The participants will be matched based on level of injury (tetraplegia versus paraplegia) and time since injury (less than versus more than 10 years) using block randomization using a 2 × 2 design developed by the study statistician. Randomization was conducted using n-query computer program at the baseline before enrollment in the trial (Table 1). Current recruitment status is outlined in Table 2.

**Table 2 Tab2:** The breakdown of the number of persons who have been contacted for the study, who have completed the study, or are currently actively participating in the study. All others have either failed screening or withdrawn from the study

	Study period					
	Pre-Enrolment		Enrolment	Baseline	Post-intervention	
Timepoint**	1	2			1	2
Pre-enrolment:	**536**					
Not-interested	**354**					
Expressed interest	**182**					
Phone screen Failure		**68**				
Physical screen failure		**50**				
Qualified and Enrolled		**64**				
Enrolment [1 = a +b]			**64**			
No Show ^(a)^			29			
Consented ^(b)^ [2=c +d + e + F]			**35**			
Screen Failure ^(c)^			5			
Withdrawn ^(d)^			6	3	1	2
*Completed* ^*(e)*^			21			
*Currently Active* ^*(f)*^			3			
Pending future enrollment ^(g)^			13			
Total sample size [3=b +g]			**48**			
Interventions:						
[NMES+FES]			15	14	13	12
[Control + FES]			15	13	13	12
Assessments:						
[Body Composition Variables]				X	X	X
[Metabolic variables]				X	X	X
[Muscle Biopsy variables]				X	X	X
[Torque and fatigue variables]				X	X	X

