### Statistical analyses

T-tests and Pearson chi-square tests will be used to compare characteristics that may act as confounding variables, including age, level of injury, time since injury, %FM, as well as the three outcome variables (Si, Sg, VO_2_) to ensure that each group is not different with respect to each variable at baseline. A repeated-measures ANOVA will be performed with glucose effectiveness as the primary study outcome and effects for treatment group (NMES + FES versus control), time (baseline and post-interventions 1 and 2), and the interaction between the two factors included in the model. Similar repeated measured ANOVA models will be fit with each of the body composition, metabolic profile, protein expression, and ETC measures (Aim 3). All statistical analysis will be performed at the 0.05 level with SAS V9.4 (Cary, NC, USA).

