### Sample size

We have acquired pilot data for all outcomes of this project. Glucose effectiveness possesses the smallest effect size from baseline to follow-up with NMES-RT showing a mean baseline effectiveness of 0.01716 and post-treatment mean of 0.02258. Cohen’s *f* was found to be 0.271 using a sample variance of 0.0001 [25]. Assuming the correlation between the pre- and post-treatment measurements is 0.3735 and three total measurements are acquired, 38 individuals will need to complete the study at 90% power using a Type-1 error rate of 0.05. At least 48 participants will need to be recruited, adjusting for a 20% dropout rate. All sample sizes were calculated using the software G*Power (V3.1.9.2). A sample size of 24 was calculated using insulin sensitivity data without regard to dropout rate.

Other factors, such as insulin sensitivity and VO_2_, are considered; each representing larger effect sizes than glucose effectiveness (*f* = 0.313 and *f* = 0.432, respectively). Our study would result in a power of 97.51% and 99.82% for observing the baseline to follow-up difference between the NMES + FES and Control + FES groups, provided the correlation between baseline and follow-up measurements are 0.4 for the outcomes.

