There are currently no guidelines on how to maximize the benefits of FES-LEC to improve the cardio-metabolic health variables after SCI. Several strategies have been recommended to maximize the training outcomes of FES-LEC. Raising the stimulation amplitude to 300 mA has been proposed to increase the neuromuscular response and increase energy expenditure; however, this option is not FDA-approved for most of the available FES bikes [67, 68]. The maximum current on most of the commercially available FES bikes is 140 mA. Moreover, this high level of stimulation amplitude may increase the risk of developing autonomic dysreflexia. Another alternative approach is to increase the frequency of FES-LEC training to 3–7 days/week [17]. This approach is limited by poor compliance in longitudinal trials. We have studied the exercise adherence to home-based FES-LEC in 17 individuals with SCI. We have found that just maintaining a frequency of three times rather than two times/week decreased adherence from 72% in the first eight weeks to 63% in the second eight weeks [65]. A case report has shown showed that a frequency of 2–3 times per week is likely to increase adherence up to 54 months of training [69]. This is accompanied with reasonable gain in lean mass, on an average of 0.8–1.6 kg, in persons with SCI [23, 70]. Another consideration is the frequency of training and the time allowed for recovery between sessions. Our cross-sectional data showed that force remained reduced by > 20% for 48–72 h after an acute bout of FES-LEC in men with SCI [68]. This is likely caused by to exercise induced muscle damage that typically occurs as result of chronic disuse of the paralyzed muscles. It is vital to initiate appropriate mechano-stressor stimuli to optimize skeletal muscle adaptations as a large paracrine gland [71, 72]. Moreover, FES-LEC is considered an appropriate aerobic training paradigm that may stimulate an increase in mitochondrial capacity and help partitioning of substrate utilization of IMF as primary source of energy during exercise and further improved insulin sensitivity [73].

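### The repeated-measures ANOVA named for the primary outcome would, in its usual form, drop randomised participants who miss a visit; a mixed model and continued P1/P2 invitations would keep most of them

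*Protocol article*

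**What the plan says.** **Analysis.** Under Statistical analyses, the article states: "A repeated-measures ANOVA will be performed with glucose effectiveness as the primary study outcome". The model has group, time (three visits) and their interaction. On software it says "All statistical analysis will be performed at the 0.05 level with SAS V9.4"; the Data Availability section mentions SPSS 24 instead. Neither place names a procedure, an analysis set or a rule for missing visits.

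**Size.** Under Sample size, Cohen's f "was found to be 0.271 using a sample variance of 0.0001". The text continues: "Assuming the correlation between the pre- and post-treatment measurements is 0.3735 and three total measurements are acquired", and then "38 individuals will need to complete the study at 90% power using a Type-1 error rate of 0.05". Recruitment follows from that: "At least 48 participants will need to be recruited, adjusting for a 20% dropout rate".

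**Conduct so far.** The note to Table 1 says that randomisation preceded baseline testing, so every later loss is the loss of an assigned participant. Table 2 gives counts by arm at enrolment, baseline, P1 and P2, and a withdrawal row. Its caption says of everyone not completed, active or merely contacted: "All others have either failed screening or withdrawn from the study".

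**The concern.** In its conventional form, repeated-measures ANOVA needs every visit from every person. Someone who attends baseline and P1 but not P2 is removed entirely, including the data already collected. Because the sizing rests on completers and expects one in five to leave, this would not be a rare event.

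What is at stake is which effect is estimated. The closing paragraph of the Discussion looks ahead to adopting the combined programme in rehabilitation practice, for which the effect of assigning it is the relevant quantity. A completers' comparison answers a different question if leaving is related to response or tolerance. Limitations mentions non-response to stimulation and intolerance of it. During the first 12 weeks only the NMES + FES arm trains with stimulation, so reasons for leaving could differ between arms even when the numbers are equal.

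The analysis model can be changed later. Visits that never took place cannot be recovered.

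**Working it through.** **1. The plan's own figures.** Inputs from Sample size: means 0.01716 and 0.02258, variance 0.0001 (SD 0.01), correlation 0.3735, three measurements, alpha 0.05. Two groups, and sphericity assumed.

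- f = (0.02258 − 0.01716) / 2 / 0.01 = 0.271, as stated.
- Group-by-time interaction: λ = f² × N × m / (1 − ρ) = 0.271² × 38 × 3 / 0.6265 = 13.36, with (2 − 1)(3 − 1) = 2 and (38 − 2)(3 − 1) = 72 degrees of freedom. Power is 90.4%, and 38 is the smallest N that reaches 90%.
- With two measurements instead of three, the same calculation needs 47. The figure of 38 therefore presumes three visits per person.
- 38 / 0.80 = 47.5, rounded up to 48, as stated.

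**2. Who is lost (Table 2).**

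| | Assigned | Baseline | P1 | P2 |
|---|---|---|---|---|
| NMES + FES | 15 | 14 | 13 | 12 |
| Control + FES | 15 | 13 | 13 | 12 |
| Total | 30 | 27 | 26 | 24 |
| Lost since previous column | – | 3 | 1 | 2 |

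The losses match the withdrawal row (3, 1, 2; total 6).

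- Out of a three-visit comparison: 6/30 = 20%, 3 per arm.
- Of these, 3 left before baseline, so before any training and with no outcome data.
- Left after baseline: 3/27 = 11.1%; 2 of the 3 had reached P1.
- A model using all available visits would include 27 of 30; a complete-visit ANOVA would include 24.

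**3. How firm the counts are.** The 24 at P2 is 21 completed plus 3 still active. The note to Table 1 gives 23 at P1 and 20 at P2, against 26 and 24 in Table 2.

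**4. Possible size of the distortion.** Let the effect in completers be E, and treat the three active participants as completing. If the 3 post-baseline leavers contribute no effect, the average over those with a baseline is (24/27) × E, and the completers' estimate is too large by 27/24 = 1.125, or 12.5%. If leavers respond like completers, the ratio is 1. Using retention in the NMES + FES arm alone, 14/12 = 1.167; that is a difference of one or two people and should not be over-read.

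**5. Power.** At 48 recruited, 20% loss leaves 38.4, in line with the 38 required. Power is not the issue.

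**The case against.** The strongest reply is that the article is silent, not wrong. The sentence about 38 people completing is an ordinary dropout allowance and does not define who is analysed. SAS can fit a repeated-measures model with or without incomplete cases. Analysis sets and missing-data rules usually sit in a full protocol or SAP, which is not shown. This stands to the extent that the absence of an analysis set is not itself a fault. It does not remove the point that the method actually named, in its usual form, discards incomplete cases, and that a better one is readily available.

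A reader might infer several stronger things, which the documents do not support:

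- *Anyone who stops training leaves the assessments.* No such rule is stated. The declining counts sit under the interventions heading of Table 2, and the assessment rows carry only crosses. Someone who stopped training but kept attending might not be listed as withdrawn.
- *One in five stopped training.* Three of the six left before training began, so at most 3 of 27 could have done so.
- *The effect is overstated by 25%.* That is 30/24 and needs all six leavers to count as non-responders, including three never measured. Nor should it be applied to the pilot difference of 0.00542, which is a before-after change with NMES-RT and not a difference between arms.
- *The article's own adherence data predict the problem.* The Discussion reports that training three times a week "decreased adherence from 72% in the first eight weeks to 63% in the second eight weeks", but this was home-based cycling; the present trial trains twice weekly. The retention barrier that Limitations names is transport, for which help is budgeted.

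Losses are also balanced, 3 and 3, and only one person with a baseline left before P1, the phase in which the arms differ. There is thus no visible differential attrition, although equal totals do not show equal reasons.

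**Conclusion.** The point holds in a limited form. The analysis as named, taken conventionally, would leave out randomised participants with a missing visit: provisionally 6 of 30, of whom 3 have usable data. Completers-only analysis and the end of assessment on stopping training are inferred from the named method, the sizing and the counts; neither is written down.

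The possible overstatement among those with a baseline runs from none, if leavers respond like completers, to about 12.5%, if they gain nothing. This assumes that the Table 2 counts are right and that the three active participants complete. Given the conflict with the note to Table 1, both figures are provisional. The sample size reproduces and is not in question. The change is worth making because it is cheap and can still affect the 3 active and 13 pending participants.

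**What to change.** 1. Under Statistical analyses, replace the repeated-measures ANOVA for glucose effectiveness with a likelihood-based mixed model for repeated measures (group, visit, group by visit). Include every randomised participant with at least one measurement, in the arm assigned. Keep the completers' analysis as a sensitivity analysis.
2. State in the visit plan that anyone who stops training is still invited to P1 and P2 on the original week schedule, at least for the IVGTT, and that the date and reason for stopping are recorded.
3. Reconcile the P1 and P2 counts in Table 2 with the note to Table 1.

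**Cost.** Items 1 and 3 are wording and checking. Item 2 takes some visit effort, and the article does not say whether that is funded. The expected effect may be somewhat smaller than in completers.

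**Limits.** The mixed model cannot recover the 3 people with no measurement, and the one with a baseline only adds little to the group-by-visit contrast. It also assumes that missing visits are explained by the data observed, which is why item 2 matters as well as item 1.

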## Discussion

In the last 10 years, there have been significant advances in our understanding of the body composition changes and metabolic profile after SCI. Skeletal muscle atrophy is accompanied with infiltration of ectopic adipose tissue both in the paralyzed muscle and in trunk region that facilitates the development of central adiposity. In persons with chronic SCI, VAT and SAT are 58% and 48% greater than healthy able-bodied controls, respectively [56–58]. Ectopic adiposity is simply defined as storage of fat in non-adipose tissue sites and characterized by increasing the release of inflammatory cytokines. These changes in body fat distribution occur in conjunction with excessive production of hepatic glucose in the absence of autonomic nervous system control after SCI in those with injuries above the fourth thoracic segment [59]. The increase in VAT is negatively related to high density lipoprotein cholesterol (HDL-C) and insulin resistance, with men being 1.8–2.6 times more susceptible to accumulation of VAT than women after SCI [60]. Several anthropometric and imaging measurements have been proposed to accurately quantify changes in muscle size and visceral adiposity [61, 62]. Sumrell et al. have recommended SCI cutoffs for central adiposity that can simply be used to identify cardiometabolic risks using seated/supine circumferences in men with chronic SCI [62].

Today, exercise is still considered a feasible, accessible, and non-pharmacological approach that can overcome several of the cardio-metabolic risk factors after SCI. Upper extremity cycling exercise and/or circuit resistance training are limited to small muscle mass above the level of lesion and do not exercise large muscle groups in the lower extremities. Moreover, persons with tetraplegia (≥ C6 SCI) are less likely to benefit from upper extremity training at intensities that can improve cardio-metabolic risk parameters [63]. This renders exercise limited to use of the upper extremities as an ineffective method to attenuate the deterioration in metabolic profile and body composition after SCI. Another form of exercise is FES-LEC, which effectively restores muscle size and improve of cardio-metabolic risk factors after SCI [64, 65]. However, FES-LES is limited by low exercise intensity, oxygen uptake, and rapid muscle fatigue. To offset for these limitations, the use of hybrid exercise by combining both upper extremities and FES cycling has been shown to improve cardiovascular outcomes more than FES-LEC [66]. Arm cranking exercise (ACE) in combination with FES-LEC displayed increasing muscle oxygenation (StO_2_) at 40%, 60%, and 80% of individuals’ peak VO_2_ compared to ACE only that showed decreases in StO_2_ and FES-LEC only that had steady increases in just 60% and 80% peak VO_2_. The combination of ACE + FES-LEC demonstrates better oxygenation than either ACE or FES-LEC alone [66]. These forms of hybrid-FES training are more suited for high-intensity, high-volume exercise training than FES-cycling only and require intact upper extremity function.

There are currently no guidelines on how to maximize the benefits of FES-LEC to improve the cardio-metabolic health variables after SCI. Several strategies have been recommended to maximize the training outcomes of FES-LEC. Raising the stimulation amplitude to 300 mA has been proposed to increase the neuromuscular response and increase energy expenditure; however, this option is not FDA-approved for most of the available FES bikes [67, 68]. The maximum current on most of the commercially available FES bikes is 140 mA. Moreover, this high level of stimulation amplitude may increase the risk of developing autonomic dysreflexia. Another alternative approach is to increase the frequency of FES-LEC training to 3–7 days/week [17]. This approach is limited by poor compliance in longitudinal trials. We have studied the exercise adherence to home-based FES-LEC in 17 individuals with SCI. We have found that just maintaining a frequency of three times rather than two times/week decreased adherence from 72% in the first eight weeks to 63% in the second eight weeks [65]. A case report has shown showed that a frequency of 2–3 times per week is likely to increase adherence up to 54 months of training [69]. This is accompanied with reasonable gain in lean mass, on an average of 0.8–1.6 kg, in persons with SCI [23, 70]. Another consideration is the frequency of training and the time allowed for recovery between sessions. Our cross-sectional data showed that force remained reduced by > 20% for 48–72 h after an acute bout of FES-LEC in men with SCI [68]. This is likely caused by to exercise induced muscle damage that typically occurs as result of chronic disuse of the paralyzed muscles. It is vital to initiate appropriate mechano-stressor stimuli to optimize skeletal muscle adaptations as a large paracrine gland [71, 72]. Moreover, FES-LEC is considered an appropriate aerobic training paradigm that may stimulate an increase in mitochondrial capacity and help partitioning of substrate utilization of IMF as primary source of energy during exercise and further improved insulin sensitivity [73].

Surface NMES-RT has been shown to increase muscle hypertrophy, increase fatigue resistance, and improve oxygen reuptake in the muscles [20–25]. In a randomized clinical trial, Gorgey et al. used TRT in combination with NMES-RT to determine the impact on body composition and metabolic variables in men after SCI compared to a TRT-only control [25]. The study reports an almost 20 cm^2^ increase for whole thigh and absolute muscle CSA, in addition to an 8–12% decrease in VAT and marginal 15% increases in BMR for the TRT + RT group, with no changes in the TRT only group in thigh muscle CSA or BMR. The increases in lean mass and BMR combined with the decreases in VAT content after TRT + RT may improve cardiometabolic health, insulin sensitivity, and prevent obesity [25]. Moreover, we and others have shown that NMES-RT is accompanied with decrease infiltration of IMF, reduce peripheral muscle fatigue by 30%, increase muscle quality and slowness of rise time, and increase mitochondrial activity after SCI [74, 75].

### Limitations

Dietary intake may confound effects of the training and increased muscle mass. However, a recent trial showed that protein intake over an eight-week period would not trigger increase in muscle size in persons with SCI [76]. The dietary records are evaluated on a weekly basis to monitor caloric intake. Any intake that exceeds 300–500 kcal/week above their baseline BMR will be flagged. Another limitation is that close to 20% of the population may not benefit from NMES/FES applications, particularly those with lower motor neuron injury and denervation of skeletal muscles, thus limiting eligibility for enrollment and reducing the pool of patients who may benefit from NMES/FES as a therapy. Another limitation is those who do not respond to NMES due to lower motor neuron denervation (LMN) or intolerance to electrical stimulation [77]. Currently, a clinical trial is underway to test the efficacy of using long pulse width stimulation to restore muscle size in those with LMN after SCI [77].

We proposed a two-center study to facilitate recruitment of 48 participants. We have included an age range of 18–65 years, women, and those with AIS C, provided a wheelchair is their primary method of mobility, who possess no functional movement sublesionally and use non-weight bearing activities only. The feasibility of this approach may be called into question because any benefits may be lost with the cessation of training. Our protocol emphasizes long-term compliance and adherence to maximize benefits. We have tested the feasibility of home-based NMES-RT over an eight-week period utilizing video-telecommunication service. The result showed that the trained knee extensor muscle CSA increased by 18% compared to the controlled limb [78]. This may serve as a continuation of the current trial and bases for establishing future home-based clinical trials to maximize recruitment and reduce the cost associated with travel time.

Previously, the barriers of commitment to long-term intervention have been highlighted [79]. One of these barriers is transportation, which remains of a great concern regarding retention in the study. To further alleviate transportation burdens, a research technician has been budgeted to escort participants in a VA van to certain locations for study measurements.

In conclusion, the current clinical trial endeavors to increase the cardio-metabolic benefits of FES-LEC through the addition of NMES-RT. This may result in improvement of aerobic fitness and metabolic health and reduce the severity of chronic secondary health-related consequences. The study will provide mechanistic insights regarding molecular underpinnings of the benefits of the two different paradigms of electrical stimulation to chronically paralyzed muscles. One paradigm is mimicking RT using a weight-lifting approach and the other generates low tension stimulation mimicking aerobic-type training. It will be of interest to our population to understand the additive effects of both approaches on the cardio-metabolic outcome variables in persons with SCI. This could be simply integrated as an effective rehabilitation intervention in the clinical setting shortly after completion of the study.

